### Participant compensation

Participants will receive up to $300 in compensation for completing the study. Specifically, participants will receive $50 for completing V1, $25 for completing each of V2-V4, and $50 for completing V5, with a $75 bonus for completing all five study visits. Participants will also receive $1 for each daily cannabis use survey that they complete (up to $28) with a $3 bonus for each week in which surveys are completed on all 7 days (up to $12). Finally, participants can earn a $10 bonus for completing 75% (i.e., at least 21 out of 28) of the daily surveys. All compensation will be paid to the participants in cash on the day of each study visit.

### Intervention

All tDCS interventions will be delivered using the Soterix Medical 1x1 tDCS Clinical Trial system. Upon study enrollment, each participant will be randomly assigned to an active or sham stimulation group. In the active group, each participant will receive a 1.5mA stimulation over 20 minutes with a 30-second ramp-up and ramp-down time. In the sham control group, each participant will not receive any active stimulation over the 20-minute intervention apart from the ramp-up and ramp-down time. The ramp-up and ramp-down period in the sham stimulation is designed to make participants feel the same itching sensation as participants in the active stimulation group. Direct current stimulation will be delivered through a pair of carbonated silicone electrodes enclosed in an absorbent pad containing 10mL of 0.9% NaCl saline solution. For anodal stimulation of the right dlPFC, the anode electrode will be placed on F4 in accordance with the 10–20 international EEG system [39] and the cathode will be placed on the left upper deltoid. The Soterix Medical 1x1 Clinical Trial device comes equipped with site-specific stimulation codes that will be known only to one individual on the investigative team ([name]), such that all others will be blind to the assigned condition for the study duration. In the event that participants experience an AE related to study procedures, participants may be unblinded in order to facilitate follow-up care.

While tDCS is being administered, all participants will receive reappraisal training to learn to regulate their cravings. Each tDCS session entails approximately 10 minutes of psychoeducation on concepts and strategies that can help them regulate their cravings (e.g., reappraisal), followed by 10 minutes of practicing evoking negative consequences of cannabis use while viewing cannabis images. For example, during the first session, participants will be asked to briefly share their reasons for wanting to reduce their cannabis use with the research assistant, who will then outline several well-documented, long-term adverse effects of cannabis use, spanning physical, psychological, and occupational domains. Next, participants will generate a list of 3–5 specific and personally relevant negative consequences of cannabis use, which the research assistant will write down. The research team will utilize this information during each weekly visit to work with the participant during the reappraisal training. Participants are then introduced, in lay terms, to the idea of cognitive reappraisal with examples of how they may already be using this strategy in everyday life (e.g., consequences of not paying bills, sending angry texts). Next, participants are shown how they can use this strategy when they see things that remind them of cannabis (introduced as triggers) or when they have urges to use cannabis. They are given the rationale that, with practice, thinking about the negative consequences of using can help reduce cravings to use cannabis and reduce cannabis use. After the psychoeducation portion, participants will spend approximately ten minutes practicing this skill by viewing 20 images of cannabis and following instructions to passively view half of the images and verbalize their negative consequences for the other half of the images. Research assistants may ask participants to elaborate with prompts such as, “How would that make you feel if that [negative consequence] occurred?” Participants can refer to their list of negative consequences during this practice. Participants will rate how much they crave cannabis after viewing each image on a 5-point scale, similar to the ROC task (described in Primary Outcomes below).

### Measures

#### Baseline measures.

Participants will complete the following measures as part of their baseline assessment on V1. The Demographics form asks participants to provide information on their age, sex, race, ethnicity, and handedness. The Cannabis Use Disorder Identification Test, Revised Edition (CUDIT-R) is an 8-item questionnaire designed to identify cannabis misuse in the past 6 months [40]. The revised version has demonstrated comparable psychometric properties to the original scale and high rates of sensitivity and specificity in identifying cannabis misuse [40]. The Treatment Expectation Questionnaire (TEX-Q) is a 15-item questionnaire that measures participants’ expectations of medical and psychological treatments [41].

### Questionnaires

Participants will complete the following questionnaires at both their first and last study visits: The Anticipated Effects of Cannabis Scale (AECS) is a 17-item measure that assesses both positive and negative effects of cannabis that participants may expect [42]. The AECS further considers these expectancies based on the valence (positive versus negative) and arousal (high versus low) characteristics of each possible expectation [42]. The Consideration for Future Consequences Scale (CFCS) is a 12-item questionnaire that assesses the extent participants value immediate rewards over long-term consequences and has demonstrated acceptable levels of validity and reliability [43]. The DSM-5 crosscutting assessment assesses mental health domains that are relevant to psychiatric diagnoses [44]. The Emotion Regulation Questionnaire (ERQ) is a 10-item scale that measures participants’ tendencies to regulate their emotions via cognitive reappraisal and expressive suppression [45]. The Generalized Anxiety Disorder (GAD-7) is a 7-item clinical measure for assessing GAD [46]. The Patient Health Questionnaire (PHQ-9) is a measure of depression severity [47]. The Self-Report Habit Index (SRHI) is a 12-item questionnaire which assesses common characteristics of habitual behaviors [48]. The SRHI shows good evidence for reliability and validity across a range of substance use disorders, including CUD [48]. The Toronto Alexithymia Scale (TAS-20) is a 20-item questionnaire that evaluates an individual’s ability to identify and distinguish emotions [49]. The revised 20-item measure has demonstrated a three-factor structure and good internal consistency [49]. Finally, the World Health Organization Disability Assessment Schedule 2 (WHODAS 2.0) measures functioning and disability [50].

### Primary outcomes

The first primary outcome is cannabis use during the study. This will be measured through a brief daily survey. Participants will be sent a link to a REDCap survey at 8:00am daily to report on cannabis use over the last 24 hours. Participants will be asked about the amount of cannabis used, the form of cannabis used (e.g., smoked, vaped), and how the amount used compares to their typical use amount on a 5-point Likert scale, where 1 indicates much less cannabis used than usual, 3 indicates the usual amount of cannabis was used, and 5 indicates much more cannabis used than usual.

The second primary outcome is the EEG correlates of craving and regulation during the ROC task (Fig 2), which participants will complete before the first intervention session and after the fifth intervention session. The ROC task utilizes E-Prime software to present participants with a series of validated cannabis images, including pictures of the cannabis plant and images depicting various cannabis primary use methods [51]. The ROC task consists of 25 LOOK and 25 NEGATIVE trials total, presented in alternating LOOK and NEGATIVE blocks of 5 trials each (i.e., 5 LOOK trials, followed by 5 NEGATIVE trials, followed by 5 LOOK trials, etc.). During the LOOK trials, participants will be instructed to simply look at the image; during the NEGATIVE trials, participants will be instructed to think about the negative consequences of using cannabis. EEG data will be collected using a 128-lead Electrical Geodesic EEG system, with gel-based collection, sampled at 1000 Hz.

**Fig 2 pone.0328205.g002:**
[figure not shown]
Schematic representation of a single trial of the ROC task. Participants will view a fixation cross for 3 seconds before the instruction (LOOK/NEGATIVE) for participants is displayed for 3 seconds. A cannabis image will be displayed for 6 seconds, during which participants are to either look at the image (“LOOK”) or think about the negative consequences of using cannabis (“NEGATIVE”). After a 3-second fixation cross, participants will have up to 10 seconds to rate their level of craving for cannabis on a 5-point scale. Participants will complete 50 trials, comprising 25 LOOK trials and 25 NEGATIVE trials.

Our rationale for ERP component selection and labeling is grounded in the literature on emotional image processing. In picture-viewing paradigms involving affectively salient stimuli, the early neural response often overlaps with the P300 in both timing and topography. However, unlike discrete stimuli used in tasks like oddball tasks, emotional images typically evoke more complex and variable cognitive appraisal processes, leading to temporal jitter in the onset of peak neural engagement across trials. This results in a less sharply defined P300 and the emergence of a sustained slow-wave positivity that blends with the LPP over centro-parietal regions. To align with conventions in the ERP literature, we assess the P300 in the ~ 250–300 ms window and the LPP in the 600–900 ms window. Thus, mean amplitudes of the P300 (~250–300 ms following cannabis cue) and the early LPP (600–900 ms following cannabis cue) will be quantified. Additional analysis will also assess and consider frontal theta power.

The third primary outcome is self-reported levels of cannabis craving. This will be assessed using the MCQ [37], which will be administered immediately before and after each tDCS and reappraisal training session at each study visit. It will also be assessed using the ROC task on V1 and V5: self-reported levels of craving in response to cannabis images will be averaged separately across all LOOK trials and all NEGATIVE trials and compared.

### Data collection, management, and monitoring

#### Data collection.

Self-report data will be collected primarily through standardized assessments administered to participants through Yale University’s 21 CFR part 11 compliant version of REDCap. Participants will complete these measures during each study visit and all data collected will be identified by an ID number unique to each participant. EEG data will be collected through a 128-lead Geodesic EEG net, as described above.

### Data management

The principal investigators ([name], [name], [name]) will oversee data management. Only study team members who have been trained in human subject research and Good Clinical Practice will have access to the data. All data will be stored on devices that are compliant with the Health Insurance Portability and Accountability Act (HIPAA) and 21 CFR part 11 guidelines for electronic data collection and approved by the Yale Human Investigation Committee (HIC). Deidentified research data will be stored on Yale-managed study computers. Information containing identifiers (e.g., consent forms, participant contact information, master list) will be stored securely in locked filing cabinets at the Yale School of Medicine and will only be accessible to authorized research staff.

### Data monitoring

The principal investigators are responsible for monitoring data, ensuring compliance, and conducting safety reviews throughout the course of the study. Recruitment, retention rates, and availability of primary outcome data will be discussed at least once monthly.

### Data analysis

Data collected throughout this study will primarily be analyzed using SPSS software. To address the first aim of the study, reductions in cannabis use, as reported by research participants through the daily-administered REDCap surveys, will be analyzed using a multilevel modeling strategy. Multilevel modeling with maximum likelihood estimation for missing data will be used to conduct a linear analysis of daily use of cannabis using a nested hierarchical structure with both between- and within-subject predictors. The main effects of Group (i.e., stimulation versus sham) and Time, as well as the Group x Time interaction will be the primary fixed effects of interest. Daily use of cannabis will be compared across the study weeks, and multilevel models will be constructed to examine the slopes of longitudinal data across the weeks.

Statistical analysis of the EEG correlates of craving and regulation will be conducted using Netstation pipelines for ERPs and Matlab scripts for oscillatory power. Data will be filtered offline at 0.1–30 Hz. Ocular artifact correction will be performed on the mean amplitudes of each component with a specified timeframe. The components of interest for this analysis will consist of the P300, the LPP, and frontal theta power. These variables will be compared across Group (i.e., stimulation versus sham), Condition (i.e., LOOK or NEGATIVE), and Time (V1 and V5) in a series of ANOVAs. We hypothesize that active stimulation will result in heightened amplitude of the early LPP in the LATER condition, as regulation of craving is hypothesized to be enhanced, and diminished amplitude of the late LPP in the LATER condition, as arousal related to craving is hypothesized to be reduced. Further, we expect that frontal theta power will be enhanced after tDCS stimulation during the LATER condition.

For the third primary outcome, craving will be measured both pre- and post-tDCS using the MCQ [37], and active and sham groups will be compared via an ANOVA (Group x Condition x Time). Additionally, self-reported cravings elicited by cannabis images in the ROC task in both the LOOK and NEGATIVE conditions are rated on a 5-point Likert scale at baseline and post-treatment. These data will be averaged across trials and compared between groups via an ANOVA (Group x Condition x Time).

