**Methods and analysis:**

This longitudinal between-subjects study will recruit 60 participants who will each be randomly assigned to receive either active or sham tDCS. Participants will undergo 5 sessions, each spaced approximately one week apart. In session, they will receive 20 minutes of (active/sham) 1.5mA anodal stimulation over the right dorsolateral prefrontal cortex while receiving training in cognitive reappraisal. Primary outcomes include changes in cannabis use during the study, changes in electroencephalogram brain activity when viewing cannabis cues, and changes in cannabis craving intensity.

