**Discussion:**

The results of this study will inform a full-scale randomized controlled trial designed to assess the effectiveness of this intervention. More broadly, these results will add to the literature on the role of tDCS in enhancing CUD treatment.

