## Materials and methods

### Study design

This protocol is written in accordance with the Standard Protocol Items: Recommendations for Interventional Trials (SPIRIT) reporting template [36]. The present study will utilize a randomized design where participants are allocated to either an active stimulation condition or a sham control condition in a 1:1 ratio. To ensure randomization of active/sham administration across sexes, this 1:1 ratio is allocated within males and females separately. To minimize bias, both study participants and research staff running study visits will be blinded to the participant’s assigned experimental condition. This entails five weekly visits (baseline and four weekly visits thereafter), during which participants will undergo a 20-minute session of (active/sham) tDCS and reappraisal training each week. Participants will complete a self-report measure of cannabis craving [37] immediately before and after each tDCS and reappraisal training session. Before the first tDCS session on the first visit and after the last tDCS session on the fifth visit, participants will complete the Regulation of Craving (ROC) task [3,38], during which EEG activity will be recorded. In addition to the in-person study visits, beginning after the first study visit and ending at the last visit, participants will provide information on past 24-hour cannabis use through a daily survey delivered via short message services (SMS).

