**Fig 1 pone.0328205.g001:**
[figure not shown]
Notes: AECS: Anticipated Effects of Cannabis Scale; CFCS: Consideration for Future Consequences Scale; CUDIT-R: Cannabis Use Disorder Identification Test, Revised Edition; ERQ: Emotion Regulation Questionnaire; GAD-7: Generalized Anxiety Scale; PHQ-9: Patient Health Questionnaire; MCQ: Marijuana Craving Questionnaire; SRHI: Self-Report Habit Index; ROC task: Regulation of craving task. TDCS: 20 minutes of 1.5mA active/shame transcranial direct current stimulation; TAS-20: Toronto Alexithymia Scale-20; TEX-Q: Treatment Expectations Questionnaire; WHODAS 2.0: World Health Organization Disability Assessment Schedule 2. Note that questionnaire completion and the ROC task with EEG recording occur before the intervention session on V1, and after the intervention session on V5. * Daily cannabis use surveys are sent to each participant for 28 days following enrolment.

Study visits two through four (V2-V4) will be shorter visits during which participants only receive tDCS and reappraisal training and complete the MCQ before and after the intervention. Study visit five (V5) will consist of the same intervention administration and assessment of cannabis cravings as all previous visits. Additionally, participants will complete a post-intervention ROC task while EEG activity is recorded followed by post-intervention questionnaires.

At every appointment, research staff will assess for any adverse events (AEs) and record those reported by each participant in their study record. The study investigators will be responsible for determining the severity of AEs and their relationship to study procedures. Following any severe AEs that are possibly, probably, or definitely related to study procedures, research staff will consult the investigative team to determine if it is appropriate to continue study procedures. Although we do not expect any serious adverse events (SAEs), any participant who reports an SAE will be withdrawn from the trial and referred for appropriate follow-up care. Additionally, following the first study visit and until the end of the last study visit, participants will receive a once-daily survey asking about the amount of cannabis used and the form (e.g., smoked, vaped, edibles) of cannabis used in the past 24-hour window. In this survey, participants will also rate how the amount of cannabis used compares to the amount of cannabis they would typically use.

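### The daily-use model names maximum likelihood on missing-data grounds; REML handles the same incomplete data without the small downward bias in between-person variance at 60 participants (minor).

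*Protocol article*

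**What the plan says.** The Data analysis section of the protocol article fixes the method for the first primary outcome, a linear model of daily use: "Multilevel modeling with maximum likelihood estimation for missing data will be used". Missing data is the only purpose it attaches to the estimator. It names Group and Time as main effects, "as well as the Group x Time interaction will be the primary fixed effects of interest". On software it says "Data collected throughout this study will primarily be analyzed using SPSS software". It does not mention REML, a degrees-of-freedom method or the random-effects structure.

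The size of the data set comes from three places:

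- Abstract, Methods and analysis: "This longitudinal between-subjects study will recruit 60 participants who will each be randomly assigned to receive either active or sham tDCS".
- Study design: participants are "allocated to either an active stimulation condition or a sham control condition in a 1:1 ratio".
- Notes to Fig 1: "Daily cannabis use surveys are sent to each participant for 28 days following enrolment".

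The other two primary outcomes (EEG correlates and craving) are analysed by ANOVA and are not affected.

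**The concern.** ML estimates variance components as if the fixed effects were known. The number of daily surveys does not remove the resulting bias, because Group varies only between people. Group x Time is likewise judged against person-to-person variation in slope if slopes are random. For these terms the effective sample is 60 people, not 60 x 28 = 1,680 person-days. The between-person variance comes out too small, the standard errors are too narrow, and P values are slightly too favourable.

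ML and REML both use every available daily report, and both rest on missing at random. The one reason the article gives for its estimator therefore applies equally to REML, which corrects for the fixed effects. The plan accepts a known, small bias in a primary analysis for no stated gain.

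**Working it through.** The article gives no alpha, effect size, SD or dropout rate, and no figure of its own on this point to reproduce. I assume a two-sided 5% level.

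**Inputs.** N = 60 people (Abstract), 30 per arm under 1:1 allocation (Study design), up to 28 days each (Fig 1 notes). From the fixed effects in Data analysis, p = 2 between-person parameters for the intercept (intercept, Group) and p = 2 for the slope (Time, Group x Time).

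**Step 1: variance.** With balanced data, the ML/REML ratio for the variance of person-level intercepts or slopes is (N − p)/N = 58/60 = 0.967, or 3.3% too small.

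**Step 2: standard error.** √(58/60) = 0.983, or 1.7% too small.

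**Step 3: type I error.** 2·P(t₅₈ > t₀.₉₇₅,₅₈ × 0.983) = 0.0538. Using 60 degrees of freedom for the critical value gives 0.0540. REML with t₅₈ gives 0.0500.

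**Step 4: range for analysable people.** No dropout rate is stated, so 48 and 40 are assumptions (p = 2, t on N − 2).

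| Analysable N | Variance ratio | SE ratio | Type I error, ML |
|---|---|---|---|
| 60 | 0.967 | 0.983 | 5.4% |
| 48 | 0.958 | 0.979 | 5.5% |
| 40 | 0.950 | 0.975 | 5.6% |

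**Step 5: simulation.** There were 1,500 null trials per scenario, with 30 per arm, 28 days, and random intercept and slope. Assumed variances were 1.0 (intercept), 0.05 per week squared (slope) and 1.0 (residual). ML and REML were fitted to the same data sets; tests use t₅₈.

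| | Complete, ML | Complete, REML | Missing, ML | Missing, REML |
|---|---|---|---|---|
| Intercept variance | 0.961 | 0.999 | 0.952 | 0.992 |
| Slope variance | 0.0478 | 0.0504 | 0.0464 | 0.0497 |
| Residual variance | 1.000 | 1.000 | 1.000 | 1.000 |
| SE, Group x Time | 0.0702 | 0.0714 | 0.0788 | 0.0803 |
| Rejection, Group x Time | 0.050 | 0.047 | 0.059 | 0.053 |
| Rejection, Group | 0.042 | 0.039 | 0.057 | 0.055 |

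Missing means 25% of days absent at random, plus some dropout. The SE ratio is 0.0702/0.0714 = 0.983 with complete data, which matches Step 2, and 0.0788/0.0803 = 0.981 with missing days.

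The 3.3% applies to the spread of person-level intercepts or slopes including daily noise. The residual variance is not shrunk, so the random-effect components absorb the whole loss and fall somewhat further. With complete data, 0.961/0.999 = 0.962 for the intercept and 0.0478/0.0504 = 0.948 for the slope.

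The Monte Carlo standard error of each rejection rate is about 0.006. The simulation therefore confirms the direction of the variance bias and the SE ratio, but does not measure a 0.4-point excess in type I error.

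**The case against.** The strongest objection is that the phrase is about missing data, not about ML against REML. In a condensed article it may mean only that incomplete records are analysed by a likelihood method rather than deleted or imputed. REML fits that description too, and the estimator option could be settled in an analysis plan that is not shown. This largely stands, and it is why the point is minor. It does not remove the point: the text names an estimator, and its literal reading is the one with the bias.

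The effect is also small. A variance estimated on 58 degrees of freedom has a sampling coefficient of variation of √(2/58) = 18.6%. A 3.3% bias is 3.3/18.6, or less than one fifth, of that. This stands.

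A reader might infer more in four ways, none of which the document supports:

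- **That biased variances will size the full-scale trial.** The Abstract says only "The results of this study will inform a full-scale randomized controlled trial designed to assess the effectiveness of this intervention", and the closing paragraph of the Discussion speaks of preliminary data. Neither mentions variance components. If they were used with the SD shrunk by √(58/60), the next trial would plan 61 instead of 63 per arm at d = 0.5, or 169 instead of 175 at d = 0.3. True power would be about 0.79 instead of 0.80.
- **That covariates make it worse.** Four between-person parameters would give 5.8% at 60 people and 6.1% at 48. The article names no covariate and no dropout rate. A covariate entered only as a main effect would not use up degrees of freedom for the slope.
- **That the test runs near 6%.** With a normal reference ML gives 5.9%, but REML gives 5.5% with the same reference. Only about 0.4 points come from ML, and the article does not specify a normal reference.
- **That all primary tests are affected.** Only the daily-use model is.

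**Conclusion.** The point holds as a minor one. On the literal reading, with 60 analysable people and only the named fixed effects, between-person variance is about 3.3% too small and the affected standard errors up to about 1.7% too small. A nominal 5% test runs at about 5.4%.

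These figures assume a two-sided 5% level, a t reference and balanced data. For Group x Time they also assume a random slope, which the article does not state; without one, that term is not judged against between-person variation and the effect on it largely disappears. If the authors already intend REML, only the wording needs correcting. An excess of this size would be unlikely to change a pilot's conclusion, but it is systematic and avoidable.

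**What to change.** In Data analysis, replace the sentence on estimation with one saying that the daily-use model is fitted by restricted maximum likelihood with Satterthwaite or Kenward-Roger degrees of freedom. State separately that incomplete daily reports are handled under missing at random. Keep ML only for comparing models that differ in their fixed effects. If any variance components from this pilot are later used for planning, take them from the REML fit.

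The cost is one sentence and one software option. Standard errors become about 2% wider (√(60/58) = 1.017). No extra data are needed, and the change should be recorded before unblinding.

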### Participants

#### Eligibility criteria.

Participants will consist of 60 adults between the ages of 18 and 50 years who reside in the Greater New Haven area in Connecticut, USA and meet criteria for moderate or severe CUD. Diagnostic criteria for CUD will be assessed during screening procedures utilizing a symptom checklist based on the Diagnostic and Statistical Manual for Mental Disorders, 5^th^ Edition (DSM-5) criteria for CUD. Participants must meet at least four of these criteria to be eligible for the study. Additionally, participants must be looking to reduce their cannabis use and must have a positive urine toxicology screen for metabolites indicating regular cannabis use. Participants must also have the capacity to provide informed consent for the study.

Participants may be excluded from the study for several reasons. First, participants may not be receiving any other form of treatment for CUD while they are participating. Lifetime history of serious neurological (e.g., dementia, multiple sclerosis, tumors) or psychiatric (e.g., psychosis, bipolar disorder) conditions, strokes, or losses of consciousness will preclude participants from being eligible. Participants will also be excluded if they have a current medical history of non-CUD substance use disorders. Several contraindications to tDCS will also prevent participants from safely participating, including the presence of metallic implants or electronic devices (e.g., heart pacemakers), any history of seizures, and pregnancy or a plan to become pregnant during the duration of the study. Finally, participants will be excluded for endorsing suicidal or homicidal thoughts, using nicotine equivalent to one pack of cigarettes per day or more, or using exclusionary substances, including amphetamines, benzodiazepines, methamphetamine, cocaine, and opioids. Participants who primarily use cannabis in the form of edibles will be excluded, as the ROC task for CUD utilizes cannabis images related to smoking and vaping and does not include pictures of edibles.

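### The daily-use model treats the Group main effect as primary but names no baseline covariate; prespecifying the V1 CUDIT-R score would be a cheap gain in precision for that effect

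*Protocol article*

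**What the plan says.** The Data analysis section of the protocol article describes a linear multilevel model for daily use, fitted by maximum likelihood. On the effects it says: "The main effects of Group (i.e., stimulation versus sham) and Time, as well as the Group x Time interaction will be the primary fixed effects". It refers in general terms to predictors at both the between-person and the within-person level, but Group is the only between-person predictor it names. It also plans to examine slopes across the study weeks.

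The design facts that bear on this are:

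- Size and allocation: the trial "will recruit 60 participants who will each be randomly assigned to receive either active or sham tDCS" (abstract, Methods and analysis), at 1:1. The only balancing factor is sex: "this 1:1 ratio is allocated within males and females separately" (Study design).
- Daily surveys start after V1 (Study design) and run for 28 days (notes to Fig 1). V1 already includes the first tDCS and training session (Participant timeline).
- Baseline severity: "The Cannabis Use Disorder Identification Test, Revised Edition (CUDIT-R) is an 8-item questionnaire designed to identify cannabis misuse in the past 6 months" (Baseline measures). It is completed at V1, and the notes to Fig 1 place V1 questionnaires before the intervention.
- Eligibility sets a floor on diagnosis: "Participants must meet at least four of these criteria to be eligible for the study" (Eligibility criteria). It also requires a positive urine screen, but sets no range for the amount used.

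**The concern.** The Group main effect is a comparison of how much people in the two arms use. Its error is made up mostly of stable differences between people, because averaging many daily reports removes most of the day-to-day noise. Extra survey days cannot reduce the stable part, but a baseline measure that predicts usual use can.

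The natural candidate, a pre-treatment value of the same daily measure, is not collected. CUDIT-R is a baseline score of cannabis misuse, already in hand for every participant before stimulation, and the article gives it no role in the analysis. With about 30 people per arm, the unused precision could matter for a level estimate that is meant to inform a full-scale trial. Choosing a covariate after the data are seen would also invite doubt about selection, which naming it in advance avoids.

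**Working it through.** **No figure of the plan to reproduce.** The article gives 60 participants without alpha, power, effect size, SD or dropout. Everything below except 60, 1:1 and 28 days is an assumption.

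**Step 1: how much of the error is between people.** With intraclass correlation ICC, and day-to-day errors taken as independent, the variance of a person's 28-day mean is ICC + (1 − ICC)/28 in units of the daily variance. The stable share is:

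- ICC 0.3: 0.3 / (0.3 + 0.7/28) = 0.3 / 0.325 = 92%
- ICC 0.5: 0.5 / (0.5 + 0.5/28) = 0.5 / 0.518 = 97%
- ICC 0.7: 0.7 / (0.7 + 0.3/28) = 0.7 / 0.711 = 98%

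**Step 2: power for the level contrast.** Inputs: n = 30 per arm, two-sided 5%, illustrative difference d = 0.6 SD of the person mean, and ρ the correlation of CUDIT-R with that mean. Adjustment multiplies the residual variance by 1 − ρ². The noncentrality is d/√(1 − ρ²) × √(30/2), with 58 degrees of freedom unadjusted and 57 adjusted.

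| ρ | 1 − ρ² | Noncentrality | Power |
|---|---|---|---|
| 0 (unadjusted) | 1.00 | 0.600 × 3.873 = 2.32 | 62.8% |
| 0.2 | 0.96 | 0.612 × 3.873 = 2.37 | 64.5% |
| 0.3 | 0.91 | 0.629 × 3.873 = 2.44 | 66.8% |
| 0.4 | 0.84 | 0.655 × 3.873 = 2.54 | 70.3% |
| 0.5 | 0.75 | 0.693 × 3.873 = 2.68 | 75.1% |

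For d = 0.5, power goes from 47.8% to 59.4% at ρ = 0.5. The difference detectable with 80% power falls from 0.74 SD to 0.70 at ρ = 0.3 and 0.64 at ρ = 0.5. A gain of 5 points needs ρ of about 0.33 to 0.36 for differences of 0.5 to 0.74 SD.

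**Step 3: a second route.** Take r as the correlation with the person's true usual level and ICC = 0.5. The adjusted variance is then ICC(1 − r²) + (1 − ICC)/28. At r = 0.5 this is 0.375 + 0.018 = 0.393 against 0.518, a fall of 24%. By the normal approximation the detectable difference goes from 0.72 to 0.63 SD, as if there were 39 to 40 per arm. In a 20,000-run simulation the ratio of adjusted to unadjusted standard error was 1.01 at r = 0, 0.97 at r = 0.3 and 0.88 at r = 0.5.

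**Step 4: the slope.** A mixed model with random intercept and slope was fitted to one simulated dataset (60 people, 28 days, r = 0.5), with and without the covariate. The Group standard error fell from 0.266 to 0.247. The Group x Time estimate and standard error were the same both ways (−0.0068, SE 0.00799).

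**Step 5: chance imbalance.** The between-arm difference in mean CUDIT-R has a standard deviation of √(2/30) = 0.26 SD and exceeds 0.5 SD in about 5% of randomisations. The unadjusted standard error already allows for this.

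**The case against.** Most of the case on the other side stands, and it sets the limits of the point.

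- **The article does not exclude covariates.** It lists the effects of interest, not the full model, and a covariate list is commonly left to an analysis plan that is not shown. A reader might infer that the model will be run without any baseline covariate. The text supports only that none is named.
- **CUDIT-R is not the only candidate.** The DSM-5 symptom count from screening, the MCQ and ROC craving ratings before the V1 session, and the SRHI are also available before treatment. CUDIT-R is a reasonable choice because it scores cannabis misuse directly, but the article gives no ranking.
- **The stated hypothesis concerns reductions in use.** It therefore rests mainly on Group x Time, where Step 4 shows no gain. The reply is only partial: the article gives Group the same standing, and with no pre-treatment day recorded, an early separation between arms would appear as level rather than slope.
- **The figures hold for one form of the outcome and one coding of Time.** They describe a 28-day mean. In a model with Group x Time, the Group coefficient equals that contrast only if Time is coded suitably (for example, centred). The survey also asks for use relative to the person's own usual amount. Stable differences in amount need not carry into that item.
- **The correlation may be small.** CUDIT-R covers misuse over 6 months rather than daily amount, and the sample is restricted to moderate or severe CUD. At ρ = 0.2 the gain is under 2 points; at zero correlation the standard error rises by about 1%.

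**Conclusion.** The point holds as a precision improvement. The Group main effect is declared primary, no baseline covariate is named for it, no pre-treatment daily use exists, and a baseline severity score is collected without a stated use. Under the assumptions shown (30 per arm with no dropout, 0.6 SD, two-sided 5%), prespecifying CUDIT-R is worth about 2 to 12 percentage points of power for the Group effect at correlations from 0.2 to 0.5, and essentially nothing for Group x Time.

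A reader might go further and conclude that chance imbalance in severity biases the planned comparison. It does not: under randomisation the unadjusted estimate is unbiased and its standard error covers such imbalance, so validity is not in question. In a pilot this is a cheap, low-priority improvement and not a mistake in the plan.

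**What to change.** In the Data analysis section, add one sentence that prespecifies the V1 CUDIT-R total score, centred, as a between-subject covariate in the multilevel model of daily cannabis use. Report the model without it as a sensitivity analysis. If the analysis plan already names a baseline severity covariate, a reference to it is enough.

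The cost is one degree of freedom and no new data. The downside is a negligible gain if CUDIT-R turns out to be only weakly related to daily use in this sample. The article states that recruitment had not begun, so on that footing the sentence can be added before any outcome data exist.
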